## Abstract

**Background:** The combination of eating disorder (ED) and the experience of childhood trauma leads to significant impairment and suffering. To improve treatment, it is critically important to study treatment effects, and the mechanism of these effects. The overall aim of the current project is to; (1) build knowledge on how to best treat patients with ED with and without childhood trauma, (2) develop our understanding about how change happens for these patients. We will do this by comparing two treatment models in an inpatient setting; Compassion-Focused Therapy (CFT) and cognitive-behavioral therapy (CBT) for ED. This paper describes the development, design and implementation of the trial.

**Methods and Design:** Patients included in this randomized controlled trial will satisfy DSM-5 criteria for ED and approximately half of the patients will in addition have a history of childhood trauma. A total of 144 patients who have received either CFT or CBT are followed up 1 year after completion of the treatment. The study will collect a rich dataset of outcome measures at four time points, and process and sub-outcome measures at 13 time points. All patients will be assessed with the same clinical instruments based on current state-of-the-art methods. The primary outcome will be change in the severity of ED features as measured by the global ED examination score, and having a global ED examination score less than one standard deviation above the community mean, while secondary outcomes will relate to treatment effects on trauma symptoms, general symptoms, and quality of life.

**Discussion:** This trial will make an important contribution to the need for evidence of effective treatment for patients with ED with or without childhood trauma.

**Ethics and Dissemination:** The project is approved by the South-Eastern Regional Committee for Medical and Health Research Ethics of Norway (REC;2014/836).

**Clinical Trial Registration:**
ClinicalTrials.gov, http://www.Clinicaltrials.gov/ct2/show/NCT02649114.

## Introduction

Eating disorders are severe mental disorders (Hudson et al., 2007; Jenkins et al., 2011; Mitchison et al., 2012; Stice et al., 2013). In the fifth edition of the diagnostic and statistical manual of mental disorders (DSM-5) (American Psychiatric Association [APA], 2013) there are five EDs: (a) AN, (b) BN, (c) BED and two categories derived from the previous diagnosis ED not otherwise specified (d) other specified feeding or eating disorder (OSFED), and (e) unspecified feeding or eating disorder (USFED) (Attia et al., 2013).

The treatment research on EDs has focused on BN and, more recently, BED. Studies of high quality treatment for OSFED and AN are limited. This is a challenge, as OSFED has been the highest prevalent ED diagnosis in routine clinical practice (Fairburn and Bohn, 2005; Machado et al., 2007).

Clinical guidelines recommend cognitive behavioral therapy (CBT) as the psychological treatment of first choice, specifically for BN, and BED (National Collaborating Centre for Mental Health, 2004; American Psychiatric Association [APA], 2006). There are few specific therapy recommendations for AN due to the scarcity of conclusive outcome data for these patients. Clinical aims in CBT include decreasing the core beliefs about low self-worth and compensatory beliefs about the need to control food intake, body weight, and shape. Use of stimulus-control procedures to reduce the frequency of disordered eating, is central (Waller et al., 2007). Thus, the aims of CBT are behavioral change and changes in mood and cognitions. Studies, systematic reviews, and meta-analyses show promising effects of CBT for BED, and intermediate effects for BN, but the methodological quality of studies is low to moderate (Hay, 2013; Spielmans et al., 2013).

However, up to 50% of patients with ED do not recover after CBT (Wilson et al., 2007). The highest probability of poor treatment outcomes in patients with ED has been observed in those who experienced childhood sexual abuse and exposure to violent acts at an early age (Mahon et al., 2001; Rodriguez et al., 2005). A study showed that the risk of dropout or relapse rates was, respectively, 10 and 3 times greater among patients with ED who reported previous traumatic events compared with those patients without a history of trauma (Rodriguez et al., 2005). Our own study revealed that childhood sexual abuse and avoidant personality disorder predicted non-response course for patients with longstanding ED who received CBT (Vrabel et al., 2010). Considering the poor outcome and high dropout and relapse rates for these patients, there is a need to develop treatments tailored for patients with ED with trauma histories. To date, however, no treatment approaches for this population have been empirically tested.

When individuals endure early experiences of traumatic experiences they can become more prone toward self-criticism and to develop shame, a hurtful emotional condition characterized by perceiving oneself as a failure (Gilbert, 1998). They may try to regulate their feelings of inadequacy with strategies which ease their pain for a limited time. Accordingly, ED symptoms such as restriction, binging, and compensating behavior such as purging and excessive exercising, could be viewed as efforts to protect themselves and to control underlying feelings of shame (Goss and Gilbert, 2002). ED symptoms are effective at reducing shame in the short-term, but ultimately intensify these feelings in the long-term (Goss and Allan, 2009). Studies have shown that shame and self-criticism have been shown to be a major vulnerability and maintaining factor both for ED and posttraumatic stress disorder (PTSD) (Lee et al., 2001; Irons and Gilbert, 2005) and decreased self-criticism and increased self-compassion has been found to be particularly beneficial in reducing psychological distress and improving well-being (Lutz et al., 2004; Gilbert, 2007; Hoffart et al., 2015). CFT is a transdiagnostic psychotherapeutic approach that seeks to help shame-prone highly self-critical individuals to improve an attitude of inner-kindness and self-compassion (Gilbert, 2005, 2010). Indeed, this treatment should therefore be particularly suitable for a population with ED and childhood trauma.

There is some evidence that indicate that CFT could be beneficial for patients with ED, however, only three studies to our knowledge have investigated the treatment in ED patients. The first study, found that a 3-week self-compassion intervention reduced binge eating and weight and shape concerns among individuals with BED (Kelly and Carter, 2015). In the second study, Gale et al. (2014) examined the effectiveness of a CBT group outpatient treatment where CFT were integrated in the treatment, for individuals with AN, and BN. A large proportion of the patients experienced clinically significant improvements in ED symptoms after the treatment. At last, the third study found that a group-based CFT combined with evidence-based outpatient treatment as usual for ED generated greater improvements in self-compassion, fears of self-compassion, fears of receiving compassion, shame, and ED pathology after treatment than treatment as usual alone (Kelly et al., 2017).

Summed up, these studies support the application of CFT to the ED. However, the studies are either brief, self-help in nature, examine individuals with BED only, have small samples, or examine CFT that is offered in conjunction with other treatments. As such, only tenuous conclusions can be drawn about the benefits of CFT for individuals with ED across diagnostic subtypes. Clearly, there is a need for a randomized controlled trial to test the efficacy of CFT for this population.

A general critique of psychological treatments is that “after decades of psychotherapy research and thousands of studies, there is no evidence based explanation for how or why even our most well-studied interventions produce change, that is, the mechanisms through which treatments operate” (Kazdin, 2009). This criticism is also valid for EDs, especially patients with EDs and childhood trauma. Therefore, it is a need for more research into the therapeutic qualities and interventions that are most associated with good outcomes, both at termination of therapy, and after a follow-up period. In particular, it would be helpful to know whether it is the quality of the therapeutic alliance or the specific process, e.g., self-compassion or cognitions that alleviate ED symptoms.

The proposed study is a randomized controlled trial, comparing outcome, and mechanisms of change in CFT and CBT for patients with ED, with and without childhood trauma. Outcome is examined in terms of ED symptom severity, trauma symptoms, general symptoms, and quality of life. The studied mechanisms are self-compassion, cognitions and alliance. Mechanism variables will be measured repeatedly (weekly) over the course of treatment.

### Objective

The first objective of this study is to assess the relative effects CBT and CFT in terms of recovery from ED defined as change from baseline to post-treatment in the global score of EDE. The mean scores in the two intervention groups are compared. The second objective is to assess whether – for patients with trauma compared to those without – CFT is more effective in (i) reducing ED psychopathology, (ii) reducing general symptoms and trauma symptoms, and (iii) improving health-related quality of life. The third objective is to examine the process of therapy by assessing self-compassion, cognitions, and alliance repeatedly over the course of treatment to examine their possible predictive and mediating effects on treatment outcome.

## Methods

### Design

This research project involves a randomized controlled trial using a naturalistic sample of patients with ED, with and without childhood trauma. Patients will be randomly assigned to CFT or CBT. Every 3–4 months (from January 2015 – January 2019), 16 new patients will be admitted for 13 weeks of inpatient treatment in ED Unit at Modum Bad Hospital. Assessment on the overall outcome measures will take place at the pre-care evaluation, at admission, discharge, and 12-month follow-up. The weekly outcome and process measures will be completed every Monday. The present study protocol was written in accordance with the standard protocol items: recommendations for interventional trials (SPIRIT) (Chan et al., 2015) (see Figure 1 and Supplementary Material).

**FIGURE 1 F1:**
[figure not shown]
The figure illustrates the recruitment, screening, and randomization of participants to the project. Exclusion and inclusion criteria are reported in the text.

### Participants

Potential participants will initially be evaluated by a team of independent psychologists and psychiatrists who have been trained and have experience in diagnostic assessment. Consensus discussions with an experienced therapist will be used in the case of diagnostic ambiguity. Those who meet criteria for admission into the program will be put on a waiting list. The average waiting time between the pre-care evaluation and the admission evaluation is projected to be 10–15 weeks.

#### Inclusion Criteria

In order to be eligible to participate in this study, a participant must meet all of the following criteria: (1) adult inpatients (from age 18 years) with an ED diagnosis: AN, BN, and OSFED (EDNOS), according to the eating disorder examination-interview and (2) provision of informed consent.

#### Exclusion Criteria

A potential participant who meets any of the following criteria will be excluded from participation in this study: (1) current suicidal risk or psychosis that need extensive care, (2) serious substance abuse interfering with treatment, or (3) ongoing trauma (e.g., current involvement in an abusive relationship).

### Randomization

Patients will complete the baseline measures and after having signed an informed consent, a researcher blind to the study condition will conduct the random assignment procedure. A blocked randomization procedure will be used to ensure that there will be assigned an equal number of patients with trauma and non-trauma to each condition. Hence the blocks are in pair, such as two trauma patients and two non-trauma patients will be randomly assigned to each condition. The probability for each patient to end up in any of the two conditions will be kept constant at 0.5.

Researchers in the study will be blind to trauma category and the patient’s allocation to the groups. Because of the nature of the treatment content and procedures, therapists, and patients will not be blinded to the group allocation. Patients are informed about their group allocation after completing the pre-care evaluation.

### Statistical Methods

We will conduct independent *t*-test with the continuous variables and chi-square test with the categorical variables to check for differences at baseline. Treatment differences will be analyzed using hierarchical linear modeling (HLM; (Raudenbush and Bryk, 2002), hence all available data will be used. Thus, a patient with only data at admission can be included in an analysis and contribute to the estimation of model parameters (Kwok et al., 2008). Effect sizes (Cohen’s *d*) for HLM-analysis will be performed according to Feingold (2009). Interpretations will be based on the categorization of Cohen (1988).

Frequent longitudinal measurements in the treatment period will be analyzed disaggregating between patient effects (i.e., a patients standing relative to other patients) from the effect of individual patients development throughout therapy (i.e., a particular patients deviation from that patients expected level at a specific time point) using longitudinal mixed models (Curran and Bauer, 2011). This disaggregation is able to examine intra-individual process of change that is not contaminated with between-person variability (Paccagnella, 2006; Enders and Tofighi, 2007; Curran and Bauer, 2011). Within effects gives information on the level of the individual patient, making research findings directly applicable for therapists working with a specific patient.

Moderator variable will be included to analyze whether any treatment effects are modified by trauma or ED diagnosis. If treatment arms do not differ in outcome, combined latent class growth curve modeling will be conducted to analyze reasons for individual differences at baseline and in the rate of change across time. The multiple imputation procedure in SPSS will be used to impute missing data, if the data is missing at random.

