### Power Estimation

A lower-bound probability of detecting effects in clinical research (power) of 0.80 has been suggested (Cohen, 1988). To get some idea of the statistical power in the present study, we estimated the necessary number of observations (*n*) for achieving a power of 0.80 of detecting a medium effect (Cohen’s *d* = 0.5) using an alpha level of 0.05 for three common tests: Calculations of statistical power were performed with G^∗^Power (Buchner and Erdfelder, 1996). All other statistical analyses were conducted with SPSS.

The primary outcomes in the two groups were compared using analysis of covariance (ANCOVA) with pre-treatment values as the covariate. Making the conventional assumptions of no treatment by pre-treatment interaction, this may be formulated as:

(1)$${\text{Post}}_{\text{i}}=\alpha +\beta_{1}^{*}{\text{Treatment}}_{\text{i}}+\beta_{2}^{*}{\text{Pre}}_{i}+\varepsilon_{\text{i}}$$

The treatment-effect may be estimated by the increase in explained variance when including the Treatment effect in the model. Using *d* = 0.5 this corresponds to an increase in *R*^2^ of 0.06. Assuming a rejection criterion (alpha) of 0.05 and a desired power of 0.80 of detecting an increase in *R*^2^ of 0.06, the estimated required sample size is 62 patients per treatment condition.

The design also included a dichotomous “trauma” condition (see section “Introduction”). Reasoning as above the model may be formulated as:

(2)$${\text{Post}}_{\text{i}}=\alpha +\beta_{1}^{*}{\text{Treatment}}_{\text{i}}+\beta_{2}^{*}{\text{Trauma}}_{\text{i}}+\beta_{3}^{*}{\text{(Treatment}}_{\text{i}}^{*}{\text{Trauma}}_{\text{i}}\text{)}+\beta_{4}^{*}{\text{Pre}}_{i}+\varepsilon_{\text{i}}$$

The effect of interest, the Treatment by Trauma interaction, will be estimated by the increase in explained variance when including this effect in the model over a model with all other effects included. Assuming a rejection criterion (alpha) of 0.05 and a desired power of 0.80 of detecting an increase in *R*^2^ of 0.06, the estimated required sample size is 64 patients per treatment condition. The statistical power of the present study with total *N* = 144 thus appears adequate.

As there seems to be no single standard for power analysis within disaggregating between patient effects from the effect of individual patients using longitudinal mixed models, we did not conduct further power, or sample size for this analysis.

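### The within-patient process effect is an average over patients, but the protocol reads it as directly applicable to a specific patient and states no analysis of how far patients differ

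*Protocol article*

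**What the plan says.** The third aim in the Objective section of the protocol article is to study self-compassion, cognitions and alliance over the course of treatment as predictors and mediators of outcome. Statistical Methods assigns the weekly data to mixed models that split each process measure in two: the patient's standing relative to other patients, and "a particular patients deviation from that patients expected level at a specific time point". The paragraph ends with the interpretation at issue: "Within effects gives information on the level of the individual patient, making research findings directly applicable for therapists working with a specific patient".

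The Abstract gives the size of the data set: "A total of 144 patients who have received either CFT or CBT are followed up 1 year after completion of the treatment", with "process and sub-outcome measures at 13 time points". For this analysis the Power Estimation section says "we did not conduct further power, or sample size for this analysis".

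Two other planned analyses deal with differences between patients. Trauma and eating-disorder diagnosis are to be tested as moderators of treatment effects. If the arms do not differ, a latent class growth model is to explain differences in baseline level and rate of change.

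**The concern.** Centring a process measure on each patient's own expected level removes differences between patients in level. It does not remove differences in slope, that is, in how strongly symptoms follow the process measure within a patient. The fixed coefficient averages those slopes, and its null hypothesis is that the average is zero. Moving from that average to one patient requires slopes that are alike, or at least nearly all of one sign, and no stated analysis looks at this. The moderator analysis concerns the effect of treatment. The growth-class analysis concerns symptom trajectories and is run only if the arms do not differ.

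The article's own design gives no ground to presume similar slopes. The sample mixes three diagnostic groups, patients with and without childhood trauma, and two therapies. The CBT arm is built on an individual formulation of what maintains each patient's disorder.

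At stake is what the process results may be used to tell therapists. A mean association could be passed on as a statement about the patient being treated, while patients with no association or the reverse one go unseen.

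**Working it through.** **The plan's own figure.** There is none for this analysis. The sample sizes in Power Estimation (62 and 64 per arm) belong to the treatment effect and the treatment-by-trauma interaction. An R² increase of 0.06 gives f² = 0.06/0.94 = 0.0638 and a total of 125, or 62.5 per arm, within two patients of both figures. They do not bear on the point here.

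**Inputs.** From the Abstract: n = 144 patients, T = 13 occasions. From Power Estimation: alpha 0.05, taken as two-sided. Assumed, because the article gives no values: patient slopes normal with mean m and SD τ; within-patient predictor SD and residual SD both 1; complete data.

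**Step 1: share of patients with the opposite sign, and strength of the average.** The share is Φ(−m/τ). The 95% range of patient slopes is m ± 1.96τ. One patient's slope has sampling variance 1/(T − 1) = 1/12, so the correct standard error of the mean is √[(1/12 + τ²)/144], and the expected z is m divided by it. For m = 0.10 and τ = 0.2: SE = √[(0.0833 + 0.04)/144] = 0.0293, z = 0.10/0.0293 = 3.4, share = Φ(−0.5) = 31%.

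| m | τ | Opposite sign | 95% range of slopes | Expected z |
|---|---|---|---|---|
| 0.20 | 0.1 | Φ(−2.00) = 2% | 0.00 to 0.40 | 7.9 |
| 0.15 | 0.2 | Φ(−0.75) = 23% | −0.24 to 0.54 | 5.1 |
| 0.20 | 0.3 | Φ(−0.67) = 25% | −0.39 to 0.79 | 5.8 |
| 0.10 | 0.2 | Φ(−0.50) = 31% | −0.29 to 0.49 | 3.4 |

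At τ = 0 the share is nil. The z values already allow for varying slopes. In 4000 simulated trials with slopes allowed to vary, the mean was significant in 88% at m = 0.10, τ = 0.2.

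**Step 2: error rate of the average if one common slope were fitted.** That model's standard error is √[(1/12)/144]. It is too small by the factor √(1 + 12τ²), so the true rejection rate at m = 0 is 2Φ(−1.96/√(1 + 12τ²)). For τ = 0.2 the factor is √1.48 = 1.217 and the rate is 2Φ(−1.61) = 10.7%.

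| τ | Factor | Formula | Simulated, common slope | Simulated, slopes vary |
|---|---|---|---|---|
| 0 | 1.000 | 5.0% | 5.2% | 5.0% |
| 0.1 | 1.058 | 6.4% | 6.4% | 4.9% |
| 0.2 | 1.217 | 10.7% | 11.2% | 5.2% |
| 0.3 | 1.442 | 17.4% | 17.0% | 5.0% |
| 0.4 | 1.709 | 25.1% | 24.4% | 5.5% |

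Each simulated row is 4000 trials. Removing each patient's own time trend gave similar common-slope rates: 6.5%, 10.5%, 15.6% and 23.0% at τ = 0.1 to 0.4. At τ = 0.3, the rate was 16.9% with 11 occasions (two of the 13 weeks are spent at home) and 17.7% with a predictor autocorrelated at 0.5. A check with a full mixed model at τ = 0.3 gave 13% with a common slope and 3% with a random slope; with only 150 runs it is imprecise.

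**The case against.** The strongest reply is that the article names only longitudinal mixed models, which can carry random slopes, and that random-effects structure is commonly left to a full protocol or analysis plan not shown here. This stands. A reader might infer from the text that one common slope will be fitted and that the test of the process effect is therefore anti-conservative. The article does not say so, and Step 2 describes a risk under two conditions, not a stated error.

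Second, every size depends on an assumed m/τ. This also stands. A reader might infer that a large share of patients will show the reverse effect; nothing in the article supports that, and with modest variation nearly all patients share the sign. Nor must slopes be strictly identical for the average to be a useful guide.

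Third, the sentence may mean only that the estimate is at the within-person level, free of between-person differences. That would be sound, but the sentence just before it already makes that point. The disputed sentence goes on to applicability for a specific patient, and nothing elsewhere in the article qualifies it.

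What the reply does not remove is the inference itself. With a random slope in the model, the fixed coefficient is still a mean.

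**Conclusion.** The point holds as a matter of interpretation and reporting. The claim of direct applicability to a specific patient does not follow from an average within-patient coefficient, and no stated analysis supplies the missing spread. How much this matters depends on a between-patient slope SD that the article does not give. The 2% and 31% above are illustrations under normal slopes, not bounds or estimates, and equal slopes would make the problem vanish. The raised error rate, about 6% to 24% in the simulation at slope SD 0.1 to 0.4, arises only if slopes differ and a common slope is fitted.

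A reader might also carry the point over to the main results. It does not reach them: the EDE comparison between arms and the treatment-by-trauma test do not use the within-patient process coefficient.

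**What to change.** In the longitudinal mixed model, give the within-patient effect of each process measure a random slope across patients. Report its mean together with the between-patient SD, or with a 95% range of patient-specific slopes; the implied share with the opposite sign can be added. Take these from the model's variance estimate. Counting the signs of separate patient fits would mislead, because under the assumptions above a single patient's slope has a standard error of √(1/12) = 0.29, as large as or larger than most of the slope SDs considered.

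Reword the closing sentence of that paragraph so that it claims an average within-patient effect and states its spread.

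The cost is one variance term per process measure, possible convergence checks and a wider interval for the average where slopes do differ (by the factors in Step 2: 1.06 at slope SD 0.1, 1.22 at 0.2, 1.71 at 0.4). No new data are needed.
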